### Compliance strategies and monitoring

Intervention protocol compliance strategies and compliance monitoring procedures are in place, e.g., patients keep a diary. Besides describing their health and stool condition and reporting the presence of blood in the stool, patients have to record the daily/weekly capsule intake. Additionally, they return all remaining capsules they have not taken in course of the trial to the study sites as well as all empty tubes at the end of the trial. There are no laboratory tests planned, to investigate compliance.

### Outcomes

#### Primary outcome

The primary outcome will be clinical remission at week 12 post first transfer of FMT or FMFT, defined by Mayo score ≤ 2 and without any subscore >1; additionally, patients who are unavailable at follow-up week 12 will be included as non-responders (i.e., counted no remission). The Mayo Score/Disease Activity Index (DAI) is a validated scoring system for the assessment of ulcerative colitis activity including stool frequency, rectal bleeding, endoscopic findings, and physician’s global assessment [21].

#### Secondary outcomes/safety

Secondary outcomes will be steroid-free clinical remission, clinical response (defined by a decrease in Mayo score by 3 points, with a decrease in bleeding subscore by 1 as an important patient-related outcome parameter, or absolute Mayo score of 0–1), quality of life (assessed with IBDQ), and safety (assessed by adverse events).

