### Patient population

#### Inclusion criteria

18–75 years oldWritten informed consentPrior endoscopic confirmation of active UC of at least 6 months *and* with a minimum disease extent of 15 cm from the anal vergeHaving active disease, defined with a Mayo Score between 4 and 10 and Mayo endoscopic subscore >1 at study entryMay be receiving the following drugs (subjects on these therapies must be willing to remain on stable doses for the noted times)Oral 5-ASA compounds provided the dose prescribed has been stable for at least 4 weeks prior to randomization; the dose must be stable for the first 12 weeks after randomizationAzathioprine, 6-MP, or MTX provided the dose prescribed has been stable for 8 weeks prior to randomization; the dose must be stable for the first 12 weeks after randomizationOral corticosteroid therapy (prednisone prescribed at a stable dose ≤ 20 mg/day or budesonide prescribed at a stable dose of ≤ 9 mg/day) provided the dose prescribed has been stable for 2 weeks prior to randomizationTopical therapy (foams, enema) with mesalazine or budesonide: the dose prescribed has been stable for 2 weeks prior to randomizationComplete vaccination against SARS-CoV-2 as recommended by the STIKOAbility to understand and willingness to sign informed consent document in patients whom the investigator believes can and will comply with the requirements of the protocol

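### The clinical-response definition is not nested with the primary remission definition: a patient in remission with a week-12 Mayo total of exactly 2 can count as a non-responder

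*Protocol article*

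**What the plan says.** Three sections of the protocol article bear on this.

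- **Primary outcome.** Remission at week 12 is "defined by Mayo score ≤ 2 and without any subscore >1". The Mayo score is described as "including stool frequency, rectal bleeding, endoscopic findings, and physician’s global assessment", so there are four components.
- **Secondary outcomes/safety.** Response is a 3-point fall in the Mayo score, "with a decrease in bleeding subscore by 1 as an important patient-related outcome parameter, or absolute Mayo score of 0–1". The change route is thus the fall in total together with the fall in bleeding, and the alternative route reads "or absolute Mayo score of 0–1". As worded, the alternative refers to the Mayo score and not to the bleeding subscore.
- **Inclusion criteria.** Active disease is "defined with a Mayo Score between 4 and 10 and Mayo endoscopic subscore >1 at study" entry. The total may be as low as 4, and no minimum bleeding subscore is required.

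The article nowhere says that a patient in remission is counted as a responder.

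**The concern.** Response is normally read as the weaker outcome and remission as the stronger one, so every remitter should also be a responder. Here the absolute route to response stops at a total of 1, while remission allows a total of 2. A remitter with a total of 2 must therefore qualify by the change route, and that route can fail in two ways:

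1. The bleeding subscore did not fall. If it was 0 at entry it cannot fall.
2. The entry total was 4, so that reaching 2 is a fall of only 2 points.

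A response table built on this rule could list patients who met the primary outcome as non-responders. The rule also reaches beyond remitters. A patient with no bleeding at entry can respond only by reaching a total of 0 or 1, however large the fall.

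**Working it through.** This is a check of endpoint logic. The article gives no figure to reproduce.

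**Inputs**
- Entry: total 4 to 10, endoscopic subscore above 1 (Inclusion criteria).
- Remission: total at most 2, every subscore at most 1 (Primary outcome).
- Response: (total falls by at least 3 and bleeding falls by at least 1) or week-12 total 0 to 1 (Secondary outcomes/safety), reading the falls as minimum values.
- Assumption: each of the four subscores is an integer from 0 to 3. The article does not state the range.

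**Examples** (stool frequency, bleeding, endoscopy, physician's global assessment)

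| Entry | Week 12 | Fall in total | Fall in bleeding | Remission | Response |
|---|---|---|---|---|---|
| 2, 0, 2, 2 (total 6) | 1, 0, 1, 0 (total 2) | 4 | 0 | yes | no |
| 2, 1, 3, 2 (total 8) | 0, 1, 1, 0 (total 2) | 6 | 0 | yes | no |
| 1, 0, 2, 1 (total 4) | 0, 0, 1, 1 (total 2) | 2 | 0 | yes | no |
| 3, 0, 3, 3 (total 9) | 1, 0, 1, 1 (total 3) | 6 | 0 | no | no |

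The last row shows the effect outside remission: a 6-point fall without response, because bleeding was 0 at entry.

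**Count of score states**
- Eligible entry profiles: 118, of which 28 have bleeding 0.
- Remission profiles: 1 with total 0, 4 with total 1, 6 with total 2, so 1 + 4 + 6 = 11.
- Combinations: 118 × 11 = 1,298.
- Week-12 totals of 0 or 1 always satisfy the absolute route. Only the 6 profiles with total 2 can conflict; 3 of them have bleeding 0 and 3 have bleeding 1.

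The conflicts are:
- Entry total 4 (9 profiles), where the fall is only 2: 9 × 6 = 54.
- Entry total 5 or more with bleeding 0 (23 profiles), where bleeding cannot fall: 23 × 6 = 138.
- Entry total 5 or more with bleeding 1 (28 profiles), ending with bleeding still 1: 28 × 3 = 84.
- Sum: 54 + 138 + 84 = 276 of 1,298.

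In 276 − 54 = 222 of these the total fell by at least 3, so the bleeding condition alone caused the failure.

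**Restriction to plausible courses.** In 130 of the 276 pairs at least one subscore is worse at week 12 than at entry. Excluding all such pairs leaves 276 − 130 = 146 conflicts out of 977 combinations.

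**Does the parse matter?** The sentence could also be read as a mandatory 3-point fall together with either the bleeding fall or a total of 0 to 1. From an entry total of at least 4, reaching 0 or 1 is always a fall of at least 3. The two parses therefore agree, and the count is again 276.

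**Candidate corrections**

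| Response definition | Remission without response |
|---|---|
| As written | 276 of 1,298 |
| 3-point fall mandatory, plus either a bleeding fall of at least 1 or a bleeding subscore of 0 to 1 | 54 of 1,298, all from total 4 to total 2 |
| As written, with every remitter counted as a responder | 0 of 1,298 |

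**The case against.** The strongest case on the other side has four parts.

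- **Limited reach.** Response is one of several secondary outcomes. The confirmatory hierarchy in the Statistical analysis section compares remission rates only. This stands, and it bounds the importance of the point.
- **The counts are not patient frequencies.** A reader might take 276 of 1,298, or 28 of 118 entry profiles without bleeding, as the proportion of patients affected. The article gives no distribution of entry scores, and the counts weight every combination equally, so they do not support that. This stands.
- **Impact on inference.** A reader might infer that the endpoint is uninterpretable or that the treatment comparison is diluted. Neither is shown. A response rule that demands less bleeding has a clear meaning even if it is not nested with remission. The same rule applies to all three arms, and nothing in the article allows an effect on the comparison to be calculated.
- **Condensed prose.** The article says that the analyses of secondary parameters are detailed in the full study protocol, which is not shown. That is good reason not to read the 3-point and 1-point falls as exact values; the literal reading is implausible in condensed text. It does not excuse the conflict, because the article states an explicit rule that misclassifies remitters and does not merely leave a detail out.

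A reader might also conclude that the 0–1 alternative must have been intended for the bleeding subscore. The document does not establish this. Such a change would alter the endpoint in substance: a patient whose bleeding stays at 1, or rises from 0 to 1, would respond after a 3-point fall in total. It can be put to the sponsor only as a question.

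**Conclusion.** The point holds as an inconsistency between two stated endpoint definitions, given the entry criteria. It affects remitters with a week-12 total of exactly 2; those at 0 or 1 are always responders. It also affects improved patients without bleeding at entry, who have no route to response except a total of 0 or 1.

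The size is 276 of 1,298 score combinations, or 146 of 977 if no subscore worsens, assuming a 0-to-3 range for each subscore and minimum-value readings of the two falls. How many patients this represents is unknown. The primary test and the sample size are unchanged. The definition should be corrected, but it does not threaten the trial's main conclusion.

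**What to change.** Add one sentence to the response definition under Secondary outcomes/safety: every patient who meets the remission definition under Primary outcome is counted as a responder. This alone removes all 276 conflicts.

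Separately, the sponsor should check whether the absolute 0–1 alternative was meant to apply to the bleeding subscore and, if so, correct it before unblinding. That correction would address improved non-remitters without entry bleeding. With the 3-point fall kept mandatory, it would leave the 54 combinations from total 4 to total 2 unresolved, so it does not replace the first sentence.

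The cost is one or two sentences in the outcome definition, carried through to the full protocol and analysis plan where they use the same wording. No new data are needed, and the sample size and primary analysis do not change.

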##### Mucosal inflammation

To assess mucosal inflammation, fecal calprotectin and histologic remission as further secondary endpoints will be measured at week 12 and compared to week 0. Histologic remission will be assessed using the Geboes histologic scores [22] composed of 6 different grades and the Nancy histological index [23] for evaluation of disease severity in UC.

##### Patient-reported outcome measures/health-related quality of life (HRQOL)

Subjects will complete the IBDQ at the time points specified in the schedule of events (weeks 0, 4, 8, 12, 24, 36, and 52). The IBDQ is a valid and reliable instrument used to assess the quality of life in adult patients with IBD [20]. It includes 32 questions on 4 domains of HRQOL: Bowel Systems (10 items), Emotional Function (12 items), Social Function (5 items), and Systemic Function (5 items). Subjects are asked to recall symptoms and quality of life from the last 2 weeks and rate each item on a 7-point Likert scale (higher scores equate to a higher quality of life). A total IBDQ score is calculated by summing the scores from each domain; the total IBDQ score ranges from 32 to 224.

##### Microbiome/virome profiling

The microbiome composition will be characterized based on high-throughput sequencing of amplicons of the V1V2 regions of the 16S rRNA gene. This region has a high-resolution power, and in various genera, it allows a differentiation down to the species level [24]. Analysis will be performed by sequencing on the Illumina MiSeq platform with at least 30,000 sequences per sample. Raw data will be processed with an established bioinformatical pipeline and processed data analyzed for its microbial diversity and changes in the abundance of phylotypes, genera, and families [25]. Furthermore, the donor FM will be analyzed for bacterial composition and FM and FMF will be subject to virome analysis. In brief, virus-like particles (VLPs) will be purified as previously described [26]. Libraries will be generated from VLP DNA using the TruSeq® Nano DNA Library Preparation Kit and sequenced on the Illumina MiSeq platform at a sequencing depth of 2,000,000 paired end sequences. Assemblies will be done using de novo assembly tools such as Metavelvet [27]. Identification and taxonomic classification of viruses will be performed by recently developed applications such as Metavir [28]. VLPs will also be analyzed from recipient stool and stool after FM or FMF transfer to identify if bacteriophages are transferred and established in the recipient.

##### Adverse events

To assess adverse events, the Common Terminology Criteria for Adverse Events (CTCAE) will be used.

### Stopping rules

#### Procedures for discontinuation or withdrawal of a patient

The investigator may discontinue a subject’s study participation at any time during the study when the subject meets the study termination criteria described below. In addition, a subject may discontinue his or her participation without giving a reason at any time during the study.

#### Disease worsening criteria

Interruption of treatment with the investigational medicinal product is required in the case of a worsening of the underlying disease defined as follows:
Increase in the partial MAYO score (all components excluding the endoscopic subscore) by ≥ 3 points on two consecutive visits compared to the screening visit: Visits include planned study visits as well as unplanned visits to the primary care physician, another physician, or the study site), e.g., a study visit followed by a visit to the primary care physician or 2 consecutive unplanned visits during the treatment phaseWorsening of the underlying disease that, in the opinion of the investigator’s treating physician, leads to the use of an unauthorized concomitant medicationOccurrence of acute abdomen or other clinical emergency (toxic megacolon, fulminant gastrointestinal hemorrhage, ileus, perforation, etc.)Occurrence of an acute gastrointestinal infection (e.g., CDI, CMV infection)

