## Methods/design

### Study design

This is a randomized, controlled, longitudinal, prospective, three-arm, multicenter, double-blind study to determine the safety and efficacy of repeated long-term, multi-donor FMT or FMFT compared to placebo using oral, frozen capsules in 174 randomized patients with mild to moderate active UC. The primary outcome will be clinical remission at week 12.

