#### Interruption of treatment for other medical reasons

Interruption of treatment with the IMP is required in the case of:
Occurrence of an opportunistic infection or other infections requiring hospitalizationIndication for systemic antibiotic therapy (independent of the indication)Occurrence of an acute illness which, in the opinion of the attending physician of the study group, significantly impairs the patient’s overall well-being, e.g., fever > 38.5°C persisting for more than 72 h, symptomatic anemia (e.g., shortness of breath, palpitations, weakness, fatigue)If necessary, for planned or emergency surgical procedures (not e.g. for mini-surgeries on the skin or teeth under local anesthesia or without anesthesia)

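### The 3-point worsening rule for stopping treatment cannot be met by patients who enter with a partial Mayo score of 7 or 8 (assuming subscores of 0–3)

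*Protocol article*

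**What the plan says.** Under Disease worsening criteria, the protocol article makes interruption of the study product mandatory when the disease worsens, and lists what counts as worsening. The first item is the only one based on a score: "Increase in the partial MAYO score (all components excluding the endoscopic subscore") "by ≥ 3 points on two consecutive visits compared to the screening visit". No alternative is given for patients who start near the top of the scale.

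The other items in that list are:

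- worsening that a physician considers to lead to a drug the trial does not permit;
- an acute abdomen or other emergency;
- gastrointestinal infection ("Occurrence of an acute gastrointestinal infection (e.g., CDI, CMV infection")).

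The next section, Interruption of treatment for other medical reasons, adds opportunistic infections or infections needing hospital admission, systemic antibiotics, surgery, and an acute illness that "in the opinion of the attending physician of the study group, significantly impairs" the patient's general condition.

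Two other places fix the possible starting values. Primary outcome describes the Mayo score as "including stool frequency, rectal bleeding, endoscopic findings, and physician’s global assessment", so removing endoscopy leaves three components. Inclusion criteria admit a total Mayo score from 4 to 10 with an endoscopic subscore above 1 at study entry.

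**The concern.** The score trigger is a change from screening on a scale with an upper limit, and the entry criteria let patients start close to that limit. For some of them the required rise may not exist on the scale.

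Consider two patients who both record a partial score of 9 on two consecutive visits. The one who entered at 6 must interrupt treatment. The one who entered at 7 or 8, with more symptoms from the outset, need not do so under this criterion. The case left uncovered is sustained worsening to the scale maximum without a non-permitted drug, an emergency, an infection or a significant acute illness. This concerns patient safety and even-handed use of the stopping rule. It does not touch the primary outcome, the sample size or the tests.

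**Working it through.** **Inputs**

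- Required rise in partial Mayo: at least 3 points from screening (Disease worsening criteria).
- Components of the partial Mayo: stool frequency, rectal bleeding and physician's global assessment (Primary outcome, less endoscopy).
- Eligible patients: total 4 to 10, endoscopic subscore above 1 (Inclusion criteria).
- Assumption 1: each subscore runs from 0 to 3. The article does not state the range; 0 to 4 is tried below as an alternative.
- Assumption 2: the study-entry score used for eligibility equals the screening score used as the reference for worsening.

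The article gives no figure of its own on this point, so there is none to reproduce.

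**Step 1: which starting values are eligible.** Partial = total − endoscopic subscore. With endoscopy 2 or 3, the highest partial score is 10 − 2 = 8 and the lowest is 4 − 3 = 1.

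**Step 2: which of them can rise by 3.** The maximum partial score is 3 × 3 = 9, so the largest possible rise from a screening value p is 9 − p. The criterion is reachable only if 9 − p ≥ 3, that is, p ≤ 6.

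| Screening partial p | Largest possible rise | Reachable? | Total / endoscopy at entry |
|---|---|---|---|
| 6 | 3 | only at the maximum of 9 | 8/2 or 9/3 |
| 7 | 2 | no | 9/2 or 10/3 |
| 8 | 1 | no | 10/2 |

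**Step 3: how many profiles.** The number of ways three subscores of 0–3 add up to p = 1, 2, …, 8 is 3, 6, 10, 12, 12, 10, 6, 3.

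- Endoscopy 2 admits p = 2 to 8: 6 + 10 + 12 + 12 + 10 + 6 + 3 = 59.
- Endoscopy 3 admits p = 1 to 7: 3 + 6 + 10 + 12 + 12 + 10 + 6 = 59.
- All eligible profiles: 59 + 59 = 118.
- Partial 7: 6 + 6 = 12. Partial 8: 3. Unreachable: 12 + 3 = 15 of 118.
- By total score: total 10 has 3 + 6 = 9 profiles, all unreachable. Total 9 has 6 (endoscopy 2) + 10 (endoscopy 3) = 16, of which the first 6 are unreachable.
- Partial 6: 10 + 10 = 20 profiles can meet the criterion only by reaching 9.

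**Step 4: the alternative range.** With subscores of 0 to 4 the partial maximum is 12. The highest eligible partial score is still 8, and 8 + 3 = 11 ≤ 12, so every profile can meet the criterion. The eligible profiles with endoscopy 2, 3 and 4 number 101 + 89 + 72 = 262, of which 0 are affected. The finding therefore depends on the 0–3 range.

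**The case against.** The strongest reply is that the article does not contradict itself. It lists several separate triggers, and nothing says that every patient must be able to meet each one. Any change-from-baseline rule on a bounded scale has a ceiling, and the other triggers have none. A patient with sustained severe symptoms would normally have treatment escalated, which the second trigger is meant to catch, and any patient may leave the trial at any time. That stands as far as it goes: no patient is without a mandatory stopping route, and the uncovered case is narrow. But those triggers need a physician's opinion or a different event. Moreover, the section on discontinuation or withdrawal of a patient ties the investigator's power to discontinue to the listed criteria, so it does not supply the missing score-based trigger.

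A second reply is that the rule measures worsening, not severity. Moving from 8 to 9 is one point, whereas the article also uses 3 points, on the total score, to define clinical response. It follows that any remedy must accept a smaller rise for these patients, so the level is a clinical choice. It does not follow that the most symptomatic eligible patients should have no score-based trigger.

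Third, the number of patients is unknown. That stands in full. The profile count weights all subscore combinations equally, the article gives no baseline distribution, and it describes the population as "patients with mild to moderate active UC", whereas the affected profiles occur only at totals of 9 and 10.

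**Conclusion.** The concern holds, as a minor point. If Mayo subscores run from 0 to 3 and the entry and screening scores coincide, the mandatory score criterion cannot be met from a screening partial score of 7 or 8. Both values are eligible, and no other eligible value is affected. They make up 15 of the 118 eligible profiles; the share of patients cannot be derived from the article and may be small. The affected patients depend on the remaining triggers. The rule is identical in all arms, and no effect on bias, power or the significance level is claimed.

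**What to change.** Add one clause to the first worsening criterion, for example: *or, if the screening partial Mayo score is above 6, a partial Mayo score of 9 on two consecutive visits.* Nothing changes for patients who enter at 6 or below, and 0 of the 118 profiles are then left without a reachable score criterion.

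The cost is one clause of protocol wording and possibly a few more treatment interruptions, because a rise of 2 points from 7 or 1 point from 8 would then be enough. The sponsor's clinicians should confirm the level, and in particular whether a sustained one-point rise from 8 should force interruption.

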#### Interruption of treatment for other medical reasons

Interruption of treatment with the IMP is required in the case of:
Occurrence of an opportunistic infection or other infections requiring hospitalizationIndication for systemic antibiotic therapy (independent of the indication)Occurrence of an acute illness which, in the opinion of the attending physician of the study group, significantly impairs the patient’s overall well-being, e.g., fever > 38.5°C persisting for more than 72 h, symptomatic anemia (e.g., shortness of breath, palpitations, weakness, fatigue)If necessary, for planned or emergency surgical procedures (not e.g. for mini-surgeries on the skin or teeth under local anesthesia or without anesthesia)

